**Aim**

We propose to use routinely collected health data to explore whether babies with a marker in one or both kidney/s (enlargement of the tubes that collect urine in the kidney, called pelvicalyceal dilatation) detected during pregnancy have more urinary tract infections or hospital admissions for kidney problems during childhood, compared to babies without a marker.

**Project summary**

Long term kidney disease is one of the most common illnesses of childhood causing lifelong health needs. Babies born with abnormalities in the kidney are at risk of long-term kidney disease that may require

treatment such as dialysis and kidney transplant as they grow older. Opportunities for early diagnosis and treatment of kidney disease may reduce the severity of illness over time. In some pregnancies the marker pelvicalyceal dilatation, is detected in the baby’s kidney at the antenatal ultrasound scan. The meaning of this marker for the future health of the baby (for example the risk of urine infections or hospital admissions for kidney problems) is not known. There are no consistent guidelines about how to treat babies with this condition and so the identification of this marker can lead to anxiety for families and additional tests during pregnancy and after birth. We were funded by NISCHR to study the meaning of markers of uncertain significance (Welsh Study of Mothers and Babies). The study has recruited 21,106 pregnant women, with consent to follow-up the babies in future studies. There are 150 babies in our study with the kidney marker. We did not find any associations with immediate birth outcomes such as stillbirth, premature birth or genetic problems.

We propose a prospective electronic cohort study in which we will record link the data on babies already

recruited to the Welsh Study of Mothers and Babies (WSMB) with routinely collected health care datasets in

Wales to obtain follow-up data on hospital admissions and diagnoses in primary care during childhood. We will

describe the natural history of pelvicalyceal dilatation (5-9.9mm – PCD) and compare the pattern of hospital

admissions, interventions and procedures due to renal causes and the incidence of urinary tract infection during childhood between:

1. Babies with no markers and no major congenital malformations

2. Babies with a renal marker (PCD, 5 - 9.9mm) on the 18-20 week antenatal ultrasound scan

3. Babies with congenital hydronephrosis (>10mm) on the 18-20 week antenatal ultrasound scan

The information obtained will play an important role in facilitating the development of appropriate clinical guidelines and care pathways during pregnancy and after birth, including the appropriate use of medical interventions and treatment. We plan to publish results in peer review journals.

**Background**

All pregnant women are offered a fetal anomaly scan at 18-20 weeks gestation to screen for structural

abnormalities in the fetus. In at least 5% of pregnancies, markers of unknown significance (Cardiac Echogenic

Foci, Choroid Plexus Cysts, Echogenic Bowel, Pelvicalyceal Dilatation (PCD), Mild Cerebral Ventriculomegaly,

Nuchal Thickening and Short Femur) are identified. The significance of these markers is unknown in relation to

the future health of the child, and hence subsequent management during pregnancy and after birth of the baby, as there have not been any follow-up studies that adequately address this. This has led to uncertainty among health care professionals as to whether to report these findings as part of the ultrasound scan report and how to explain the significance to women. As a result there is variation between hospitals in their clinical management^1^ and the information and follow-up care that is given to women and babies. The reporting of markers can cause unresolved maternal anxiety during pregnancy and leads to the offer of invasive procedures such as an amniocentesis and further scans for reassurance.^2^ The need for evidence-based policy on this topic led to calls for clinical research into the significance and implications of detection of all ultrasound ‘markers’ in unselected low-risk populations.^3^

We were funded by NISCHR to estimate the prevalence of individual markers at the mid-pregnancy fetal

anomaly scan, assess inter- and intra-sonographer variability in the detection of markers and set up a cohort of

pregnant women and babies that can be followed up in future studies to investigate associations between

specific markers and health outcomes (The Welsh Study of Mothers and Babies - WSMB).^4^ We successfully

recruited 21,106 pregnant women and obtained consent to follow-up of their babies in future studies by using the mother’s NHS number to access health information that is routinely collected about the mother and the baby. We found variation in the reporting of markers and set up an expert panel of radiologists and sonographers to validate the markers reported to this study.^5^ The focus of this proposed research is on PCD (pelvicalyceal dilatation 5-9.9mm) and associated health outcomes during childhood because of the clinical importance of chronic renal disease and the morbidity associated with acute episodes. Chronic kidney disease is one of the most common chronic illnesses of childhood.^6^ The majority of children with this condition will proceed to have kidney transplantation during childhood or will require lifelong medical care from adult nephrology services. The incidence and prevalence of chronic kidney disease has increased over the last five years and a proportion of patients present during infancy and childhood with congenital abnormalities.^6^ Opportunities for the early diagnosis and treatment of kidney disease may reduce the severity of illness over time.

In the WSMB, PCD (5-9.9mm) was reported in 192 babies; 94% (n=150) were confirmed by the study expert

panel. The validated prevalence of PCD (5 – 9.9mm) in our population study was 0.7% (95%CI 0.5%, 0.8%),

consistent with the lower end of the range reported in the literature (0.1% - 2.1%).^7^ This wide range is attributed to the majority of studies which were in selected populations with high-risk pregnancies and lack of consistency between studies in size and gestation used to define PCD. The significance of PCD (5–9.9mm) is unclear. There is debate about the size of PCD above which investigation is warranted due to the risk of vesico-ureteric reflux (VUR) and future urinary tract infections.^8-11^ There are no consistent data relating the size of PCD to outcomes during infancy and childhood so it is not possible to distinguish between cases with underlying pathology and those with no clinical consequences.^11-15^ Data from previous studies on natural history are usually for outcomes at birth^11,12,16-19^ and these are not comparable because of differences in the size and gestation used to define the marker between the studies. Consequently there are no consistent guidelines for perinatal and post-natal management and follow-up for this condition.

In Wales, following detection of PCD (5-9.9mm) at the 18–20 week ultrasound scan, a follow-up scan is offered

between 28 – 32 weeks, and if the dilatation is >7 - 8 mm (depending on local protocols) a scan is indicated in

the post-natal period. Congenital hydronephrosis (dilatation > 10mm) detected at the post-natal scan could

indicate VUR and/or obstruction, requiring treatment with prophylactic antibiotics or surgery. Preliminary analysis of data from the Congenital Anomaly Registry and Information Service for Wales (CARIS) showed that 58% of babies with PCD 5-9.9mm detected on antenatal ultrasound scan were followed-up at birth, and of these cases, 28% of babies had congenital hydronephrosis (PCD > 10mm). 80% of babies with congenital hydronephrosis detected on antenatal ultrasound scan (>10mm) were followed up at birth and 77% of these babies had this diagnosis confirmed on post-natal scan. Although congenital hydronephrosis is defined in Europe using the measurement of at least 10mm, local protocols indicate some hospitals use a measurement of at least 7mm to define and treat cases. There are no data on the degree of progression as determined by change in measurement between antenatal or post-natal scan or the influence of measurement error, and no information about the correlation between size of PCD and urinary tract morbidity, so it is not known whether or not the 10mm cut-off to define congenital hydronephrosis is appropriate or not.

One study set in the Netherlands investigated the incidence of urinary tract infections at age 5 – 6 years and

found no difference between babies with and without PCD (5-9.9mm).^20^ However the diagnosis of urinary tract

infection was solely by parental report with no medical diagnosis and so the question remains unanswered. No

study has compared hospital admissions for renal causes between babies with and without PCD.

The natural history and evidence for any association between PCD (5-10mm) and urinary tract outcomes in

childhood needs to be established in order to define clinical guidelines and requirements for subsequent management of pregnancy and postnatal follow-up for this condition.

**Study Design and Method**

**Study population and method**

This study will include babies born in Wales between 1st January 2009 and 31st December 2011 to mothers who consented to take part in the WSMB. All pregnant women receiving antenatal care in NHS Wales who had a mid pregnancy fetal anomaly scan provided by the NHS in Wales between 1st July 2008 – 31st March 2011 were eligible for recruitment to the study. Scan data were available for 74% of women in the study who had

singleton pregnancies (n=22,045). The maximum period of follow-up in this study will be five years, accounting for censoring by death or migration.

We will describe the natural history of PCD (5-9.9mm) and compare the pattern of hospital admissions for renal causes (using ICD10 codes N00–N99, Q60-Q64), interventions and procedures due to renal causes (using OPCS-4 codes), and the incidence of urinary tract infection (using Read codes) during childhood, in those with and without markers.

In order to carry out the analysis we will record link the babies in the WSMB to hospital admissions data and primary care data from general practices, with anonymised linkage of individual babies across the

datasets. This data linkage will be done by HIRU at Swansea University, using the SAIL databank.^21,22^ The data

contained within the databank are sensitive and HIRU have developed procedures to ensure the data is made

available for research whilst ensuring that individual confidentiality is protected, and have measures in place to ensure information governance standards are met.

**Data sources**

We will use the following datasets that are available for research use in the Secure Anonymised Information

Linkage (SAIL) databank available for research use from the Health Information Research Unit (HIRU) at

Swansea University.

1. Data for admissions to NHS hospitals is contained in the Patient Episode Database for Wales (PEDW),

produced by the collation of information from clinical coding of hospital admissions by NHS Wales Informatics

Service (NWIS) who are mandated to do this in Wales.

2. Primary care data for patients are available from participating general practices that contribute data to the

SAIL databank. These general practices provide records of primary care activity with Read codes defining the

nature of this activity. The SAIL databank currently contains records of primary care activity for approximately

50% of general practice in Wales, but it is anticipated that this coverage will increase before the start of this

project in response to on-going work by HIRU to achieve this.

3. Data on the presence of major or minor congenital anomalies is reported to a stringently and comprehensively

validated registry in Wales – CARIS.

4. Data on deaths and causes of death from the Office for National Statistics (ONS) Mortality files.

5. The Welsh Demographic Service for data on migration out of Wales.

**Outcome measures**

1. Proportion of children with any renal hospital admissions (defined by ICD-10 codes N00–N99, Q60-Q64

recorded in the primary or secondary coding position) and/or linked procedures (OPCS-4). We will define the

codes for renal ultrasound scan, micturating cystourethrogram (MCUG), Dimercaptosuccinic (DMSA) scan and

surgery for urinary tract obstruction using the Classification of interventions and procedures (OPCS-4) which is

used for the coding of operations, procedures and interventions performed in the NHS.

2. Incidence of urinary tract infections and repeat infections in children under age five diagnosed in primary care. These will be defined using Read codes for clinical activity and drug prescriptions relating to primary care

diagnosis, investigation and treatment of urinary tract infection. Read codes version 2.0 is available from the

Technology Reference data Update Distribution (TRUD) website, Department of Health, England.

3. Time to first hospital admission for renal conditions in children under age 5 defined by ICD10 codes N00 –

N99 and Q60 – 64 in the primary and secondary coding position. We will code the children who have migrated

out of Wales or who die so that we can take this censoring into account in the analysis.

4. Number of hospital admissions for renal conditions and urinary tract infections (as defined above) during

childhood, over a maximum follow-up period of five years.

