**Sample size calculations**

Prelimiunary data from the PEDW dataset for the period 1998 to 2008 linked to 329,000 live births from WECC,

showed that there was a 1% chance of a renal admission before the first birthday, increasing to 2.8% by the

fourth birthday and 3.3% by the fifth birthday. The most common reasons for renal admission in children under 5 were urinary tract infection (ICD10 N39.0), non-specific renal condition (ICD10 39.9) and hydronephrosis (ICD10 N13.3). Admissions were more common in boys than girls, with a relative risk ratio of approximately 1.6. We will compare the rates of renal admissions between the 148 children with PCD and those without a marker. There will be 80% power for detecting a hazard ratio of at least 6.2 in admissions by the first birthday and for detecting a hazard ratio of 3.5 by the fourth birthday. Whilst these are large effect-sizes this study presents a unique opportunity to describe the natural histrory of PCD.

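### The renal-admission code list has no perinatal-chapter codes, so newborn urinary infection or renal failure coded only in that chapter is missed

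*Protocol*

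**What the plan says.** Under Study population and method, the Protocol will "compare the pattern of hospital admissions for renal causes (using ICD10 codes N00–N99, Q60-Q64". Outcome measures repeats the list. Outcome 1 is the "Proportion of children with any renal hospital admissions (defined by ICD-10 codes N00–N99, Q60-Q64", with those codes "recorded in the primary or secondary coding position) and/or linked procedures (OPCS-4". Outcome 3, time to first renal admission, rests on "N99 and Q60 – 64 in the primary and secondary coding position" and has no procedure route. Outcome 4 is the "Number of hospital admissions for renal conditions and urinary tract infections (as defined above) during" childhood. No code from the perinatal chapter appears in any of these places.

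Follow-up runs for at most five years, with censoring for death and for leaving Wales. Neither Study population and method nor Statistical Analysis says that time at risk begins after the newborn period.

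Outcome 2 is separate from the ICD list. It is the "Incidence of urinary tract infections and repeat infections in children under age five diagnosed in primary care", identified by Read codes and prescriptions.

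Sample size calculations reports, from earlier linked data, a renal-admission risk of 1% by the first birthday and 2.8% by the fourth. It adds: "The most common reasons for renal admission in children under 5 were urinary tract infection (ICD10 N39.0"), followed by two other diagnoses. It does not say which code list produced those risks.

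**The concern.** The study asks whether dilatation seen before birth predicts urinary infection and renal admission in childhood, and the Background links dilatation to reflux and obstruction. The first weeks of life are part of that question. ICD-10, the classification the Protocol adopts, has a perinatal chapter that includes neonatal urinary tract infection (P39.3) and congenital renal failure (P96.0). Under the fixed list, the same infection can count at six weeks (N39.0) and fail to count at two weeks (P39.3 alone).

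In the Cox model a child affected in this way either stays event-free or is given a later first event. The admission count loses one. With few events expected in the dilatation group, single admissions carry weight. Whether a newborn admission is picked up may also depend on whether the baby's dilatation was already known, and that is the exposure being studied.

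**Working it through.** **Which routes remain for a newborn admission whose renal diagnosis is coded in the perinatal chapter**

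| Outcome | Counts if an N or Q60-Q64 code is also recorded | Counts by procedure | Counts by Read code |
|---|---|---|---|
| 1, any renal admission | yes | yes (OPCS-4) | no |
| 2, primary care infection | not applicable | no | yes, if recorded by a contributing practice |
| 3, time to first admission, and the Cox model | yes | no | no |
| 4, admission count and its model | yes | none stated | no |
| 4, infection count | not applicable | no | yes, as outcome 2 |

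I read the coding-position wording in outcomes 1 and 3 as accepting either position. Data sources puts primary care coverage at about 50% of practices, so outcome 2 is only a partial substitute for an infection diagnosed in hospital.

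**Expected events (figures from Sample size calculations)**

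- First birthday, background risk: 148 × 1% = 1.5.
- Fourth birthday, background risk: 148 × 2.8% = 4.1.

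**Size of the gap**

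The documents do not say how many admissions carry only a perinatal code. Assume that they add 2% to 20% to the first-year risk:

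- First-year risk: 1% × 1.02 = 1.02%, up to 1% × 1.20 = 1.20%.
- Fourth-birthday risk: 2.8% + 0.02% = 2.82%, up to 2.8% + 0.20% = 3.00%.
- Added events among 148 children at background risk: 148 × 0.02% = 0.03, up to 148 × 0.20% = 0.30.

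**Effect on precision**

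The stated power (80% for a hazard ratio of 6.2 by the first birthday and 3.5 by the fourth) could not be reproduced for both time points by any one method tried, because significance level, sidedness, comparator size and method are not given. That is a separate matter. Assuming 148 against 20,000 children and a two-sided 5% level, the hazard ratio detectable with 80% power moves as follows:

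| Method | First birthday | Fourth birthday |
|---|---|---|
| Schoenfeld | 9.45 to between 9.26 and 7.85 | 3.93 to between 3.91 and 3.75 |
| Pooled proportions | 4.04 to between 4.00 and 3.73 | 2.66 to between 2.66 and 2.60 |

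**Effect on the comparison**

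Let a be the perinatal-only admissions as a fraction of those captured, a2 in the dilatation group and a1 in group 1. For first-year risks, approximately:

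observed ratio = true ratio × (1 + a1) / (1 + a2)

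- a1 = a2: the factor is 1 and the ratio is unchanged.
- a1 = 20%, a2 = 2%: 1.20 / 1.02 = 1.18, so the observed ratio is too high.
- a1 = 2%, a2 = 20%: 1.02 / 1.20 = 0.85, so the observed ratio is too low.

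By the fourth birthday, if the first year makes up the same share of risk in both groups, the factors shrink to 3.00 / 2.82 = 1.06 and 2.82 / 3.00 = 0.94.

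**The case against.** The strongest reply is that the gap may hardly exist in practice. A qualifying code counts in a secondary position, and a baby with known dilatation who is admitted as a newborn may well carry one. Outcome 1 also accepts linked procedures, among them renal ultrasound and cystourethrography. Infections recorded in primary care reach outcomes 2 and 4. Hospitals may code newborn infection to N39.0 anyway. The location of neonatal renal diagnoses in the perinatal chapter comes from the structure of ICD-10 and is not stated in the Protocol. Finally, the newborn period is a small part of five years.

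Much of this stands, and it limits the point to admissions carrying a perinatal code alone. It does not close the gap. Outcome 3 and the Cox model have no procedure route, and primary care data cover only about half of practices. The secondary-code route is also likely to work better in groups 2 and 3 than in group 1, which is defined as having neither markers nor major malformations. That last step is an inference.

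**Conclusion.** The point holds in limited form. The list is stated explicitly and repeatedly, so it is a fixed choice, and the Protocol gives no reason for leaving out perinatal codes while following children through the newborn period. Neonatal urinary infection or renal failure coded only in that chapter is missed in outcome 3, the Cox model and the admission count, and in outcome 1 unless a procedure is linked.

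A reader might infer three stronger things that the documents do not support:

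- **That a newborn urinary infection can never count.** Secondary codes, linked procedures (outcome 1) and primary care records (outcomes 2 and 4) all leave a way in.
- **That the loss can be read off the stated 1% as the share of the first year falling in the first 28 days (28/365 = 7.7%).** If the 1% was produced with the same code list, it already excludes perinatal-only admissions, so any missed events are additional to it. Newborn admissions with N or Q codes are captured in any case.
- **That the hazard ratio is pulled towards 1.** Equal proportional loss leaves it about unchanged, and greater loss in group 1 would push it upwards. The direction is undetermined.

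The 2% to 20% range is an assumption, and the true addition could be close to zero. On that range the effect on precision is modest and the distortion by the fourth birthday is at most about 6% either way. This is a minor improvement that costs little.

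**What to change.** In Study population and method and in Outcome measures, add P39.3 and P96.0, in primary or secondary position, to the list used for outcomes 1, 3 and 4 and for the Cox and count models. Rerun the reference risks in Sample size calculations on the same list, so that the planning figures and the outcome match.

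The cost is two codes in a data query and one rerun of existing figures. The downside is that the reference risks, and the detectable hazard ratios that depend on them, change slightly.

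### The 'renal admission' outcome counts every ICD-10 code from N00 to N99, so genital and breast disorders qualify as renal events and the outcome is wider than the study's question

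*Protocol*

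**What the plan says.** Under Study population and method, the protocol proposes to compare "hospital admissions for renal causes (using ICD10 codes N00–N99, Q60-Q64" between groups. Under Outcome measures, outcome 1 is the "Proportion of children with any renal hospital admissions (defined by ICD-10 codes N00–N99, Q60-Q64", with the code "recorded in the primary or secondary coding position". Outcome 3 (time to first admission) repeats the range, and outcome 4 (number of admissions) refers back to it. The Statistical Analysis section carries these outcomes into the Cox model and the Poisson or negative binomial model. No N code is excluded, and no urinary-only analysis is planned.

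The Sample size calculations section gives a "1% chance of a renal admission before the first birthday, increasing to 2.8% by the" "fourth birthday and 3.3% by the fifth birthday". It reports that the commonest reasons under age 5 "were urinary tract infection (ICD10 N39.0), non-specific renal condition (ICD10 39.9) and hydronephrosis (ICD10 N13.3"). It gives no share for any reason and does not say which code list produced the rates.

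**The concern.** The Aim asks about hospital admissions for kidney problems. The named procedures are renal imaging and surgery for urinary tract obstruction, and the three named reasons for admission are all renal or urinary. Nothing in the protocol explains why the code range runs past N39.

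An analyst who follows the definition must count an admission coded for a male genital, female genital or breast disorder as renal. Because secondary positions qualify, an incidental code of that kind on an otherwise unrelated admission counts too.

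Two things are at stake. The first is the absolute risk of renal admission, which the protocol intends to pass on to parents. The second is the hazard ratio for groups 2 and 3 against group 1, which could be pulled toward 1 by events that have nothing to do with the marker.

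**Working it through.** **Inputs from the protocol.** 148 children with PCD; 21,106 women recruited; background risk 1% by the first and 2.8% by the fourth birthday; 80% power stated for hazard ratios of 6.2 and 3.5 at those ages.

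**Assumptions.** Two-sided alpha of 0.05 (not stated). Comparators 21,106 − 148 = 20,958 (not stated in the sample size section). A share f of the background hazard is non-urinary, with hazard ratio 1. The 2.8% was counted on the broad list.

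**Step 1: the plan's own figures.** Schoenfeld power is Φ(√(D·a(1−a))·ln HR − 1.96), with D = 20,958·p + 148·(1−(1−p)^HR) and a = 148/21,106. At p = 2.8% and HR 3.5, D is about 601 and power is 72.7%. At p = 1% and HR 6.2, power is 61.4%. The hazard ratios detectable with 80% power are 3.93 and 9.47. A two-proportion formula gives 2.66 and 4.04. The stated 3.5 and 6.2 are approximately matched by Schoenfeld with four comparators per case (592 vs 148), which gives 3.54 and 6.17, but the protocol does not state that ratio. The power figures in step 4 therefore compare one code list with another. They are not estimates of this study's power.

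**Step 2: hazard ratio on the broad list.** Observed HR = f + (1−f)·HR(urinary). For a urinary HR of 3.5:
- f = 10%: 0.10 + 0.90 × 3.5 = 3.25
- f = 20%: 0.20 + 0.80 × 3.5 = 3.0
- f = 30%: 0.30 + 0.70 × 3.5 = 2.75

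For a urinary HR of 6.2 the values at f = 20% and 30% are 5.16 and 4.64.

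**Step 3: absolute risk.** If 2.8% came from the broad list, the urinary risk by the fourth birthday is 1 − 0.972^(1−f). This is 2.52%, 2.25% and 1.97% at f = 10%, 20% and 30%.

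**Step 4: power, broad list vs urinary-only list.** Fourth birthday, urinary HR 3.5. The urinary-only list has the higher hazard ratio but only (1−f) of the background hazard.

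| f | Schoenfeld, full cohort | Schoenfeld, 4 comparators per case | Conditional binomial mid-p, 148 vs 20,900 |
|---|---|---|---|
| 10% | 67.3% vs 68.2% | 72.8% vs 74.9% | 90.7% vs 91.4% |
| 20% | 61.2% vs 63.1% | 65.3% vs 70.1% | 85% vs 89% |
| 30% | 54.1% vs 57.5% | 56.7% vs 64.4% | 78% vs 86% |

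At f = 10% the broad list costs about 1 to 2 points. At 30% it costs 3 to 8 points, depending on the method. By the first birthday (urinary HR 6.2), full-cohort Schoenfeld gives 52.3% vs 52.2% at f = 20%, so no loss.

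**The case against.** The strongest reply is that a mismatch of codes is not yet harm. The documents do not give f, and the commonest named reasons are all renal or urinary, which argues against a dominant genital share. This stands, and it limits what can be claimed about size.

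A reader might go further and infer that the hazard ratio is certainly diluted and power certainly lost. The documents do not support that. Dilution needs the extra admissions to be unrelated to PCD. If PCD were commoner in one sex (not documented), sex-specific genital admissions could move the crude hazard ratio the other way; the adjusted Cox model includes sex. Narrowing the list also removes events, so the net power effect is small unless f is large.

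A reader might also take the statement that "Admissions were more common in boys than girls, with a relative risk ratio of approximately 1.6" as a sign that male genital codes are being counted. It is equally compatible with sex differences in the named urinary conditions, and no breakdown by sex and code is given. It is not evidence for f.

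Nor does the code range by itself make the stated power wrong. If the planning rates used the broad list, the detectable hazard ratios already refer to the broad outcome, and the problem is one of interpretation. If they used a narrower list, planning rates and outcome differ, and f should not be taken out of the 2.8% again. The protocol does not say which case applies.

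Finally, the protocol does not itself list what lies above N39. That comes from ICD-10, the classification the protocol uses to define the outcome, so the point does not depend on a cited study or an outside figure.

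**Conclusion.** The point holds as a mismatch between the outcome's label and its code list. It affects outcome 1, outcome 3 and the admission part of outcome 4, and through them the Cox and count models. It is a rule the protocol states in more than one place, not a detail left for later. Outcome 2, urinary tract infection in primary care, is defined by Read codes and is unaffected.

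That the codes are too wide for a question about kidney problems is clear from the text. It follows that the absolute renal risk is too high for any f above 0. The shift in the hazard ratio from 3.5 to between 3.25 and 2.75, for f of 10% to 30%, rests on the further assumption that non-urinary admissions are unrelated to PCD. Power loss is only a possibility. The definition should be corrected, but nothing in the documents shows that the results would be seriously distorted.

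**What to change.** For outcomes 1, 3 and the admission part of 4, define a renal admission by the urinary-tract codes: N00–N39, any later N codes judged urinary and listed one by one, and Q60–Q64. Make the same change under Study population and method. Keep N00–N99 with Q60–Q64 as a sensitivity analysis.

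In the Sample size calculations section, state which code list produced the 1%, 2.8% and 3.3% risks. Recompute those risks and the detectable hazard ratios on the final list.

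The cost is an edit to the code list and a rerun of preliminary figures from data already linked; no new data are collected. The downside is somewhat fewer events and a lower background risk, which the recomputed detectable hazard ratios will show.
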